# 7. Quality control

## 7.1 Test kit controls

Manufacturer-supplied positive and negative test controls will be run according to the manufacturer’s instruction. For assays without positive and negative controls provided by the manufacturer, the external quality control specimen will act as control.

Internal controls incorporated by the manufacturer into the assay are useful to verify the extraction, and/or amplification, and/or detection controls, as indicated in the manufacturer’s instruction.

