## 5.5 Clinical performance panel

- Left-over whole blood or serum submitted for routine testing can be used to evaluate the assays. Clinical specimens should be stored frozen at -20°C or preferable -80°C when available until testing. Total 100 specimens: 10 spiked with 5000 ge /mL of the African wild strain, 10 spiked with 5000 ge /mL of the South American wild strain and 80 non-reactive specimens will be tested.

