## 6.4 Clinical Performance

All specimens will be tested in singlicate in a randomized blinded fashion.

The acceptance criteria for the performance as 95% agreement at 1000 ge copies / mL, and 100% agreement at all other higher concentrations and for negative specimens.

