## 7.2 External quality control specimen

The evaluating site will run a validated external control specimen. This external quality might be available from a commercial source (EVA, QCMD, see above). The 17D standard preparation in a medium (10,000 ge copies/mL) and low (1,000 ge copies/mL) concentration spiked in a YF negative test human serum should be used.

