## 7.3 Proficiency panels

A proficiency panel of 10 specimens comprised of the three YFV strains (17D, African and South American wild type strain) at high (100,000 ge copies/mL), medium (10,000 ge copies/mL) and low (1,000 ge copies/mL) concentrations and serum spiked with media from uninfected cell culture (negative control);. This panel must be run successfully for each assay by each operator before the evaluation.

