## 7.4 Limits of acceptability

All results on test kit controls and the external control specimen will be documented. If the control sample does not give the expected result, the run will be considered invalid, and the run will be repeated. All problems shall be recorded on a data sheet. The principle investigator will be responsible for carefully checking all data entry forms for legibility, accuracy and completeness.

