**8.4 Clinical Performance**

For the estimation of sensitivity and specificity of the assay under evaluation for the detection of YF nucleic acids, the results of the assay under evaluation will be compared to the expected result.

Specificity will be calculated as the proportion of true negative specimens identified by the index method compared to all negatives by the reference method. Specificity will be expressed as a percentage.

Sensitivity and specificity will be estimated with their 95% confidence intervals. The 95% confidence intervals are calculated in order to assess the level of uncertainty introduced by sample size. Exact 95% confidence intervals for binomial proportions will be calculated from the F-distribution.

The initial and re-testing results of specimens (undertaken in accordance with manufacturers instructions) will be described in the report.

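### For kits supplied without their own controls, the substitute control is YFV-positive at both levels, so no negative run control is required and contamination cannot void a run under 7.4

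*Protocol*

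**What the plan says.** Protocol 7.1 has manufacturer-supplied positive and negative controls run as the manufacturer instructs, and then gives a fallback: "For assays without positive and negative controls provided by the manufacturer, the external quality control specimen will act as control". One specimen type thus takes over two roles.

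Protocol 7.2 defines that specimen: "The 17D standard preparation in a medium (10,000 ge copies/mL) and low (1,000 ge copies/mL) concentration spiked in a YF negative test human serum should" serve as this control. The YF-negative serum is only the diluent; no level without virus is listed.

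Protocol 7.4 sets the validity rule: "If the control sample does not give the expected result, the run will be considered invalid, and the run will be repeated".

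Two acceptance decisions depend on run validity:
- **Clinical panel.** Section 5.5 says "80 non-reactive specimens will be tested". Section 6.4 adds "All specimens will be tested in singlicate in a randomized blinded fashion" and requires "100% agreement at all other higher concentrations and for negative specimens". Under 8.4, "the results of the assay under evaluation will be compared to the expected result".
- **Limit of detection.** Section 8.3 fits a probit model to five replicates per level and makes a limit of 1000 ge copies/mL or lower a condition for WHO listing.

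**The concern.** A positive control and a negative control answer different questions. The first shows that a run can detect virus that is present. The second shows that a run does not report virus that is absent. Section 7.1 hands both tasks to a specimen that can perform only the first. For the kits concerned, the rule in 7.4 then protects against failed amplification but not against carry-over or contaminated reagents.

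The resulting error can go either way. Contamination in the clinical panel counts against the assay as false positives. Contamination in the low dilutions of the LoD panel counts in its favour, because missed replicates become detections and the estimated limit falls. In neither case would a required control result show that the run, rather than the assay, was at fault.

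**Working it through.** The plan states no figure on this point, so there is none to reproduce. The check is mainly a reading of the sections side by side, followed by a small calculation of what a negative control would add.

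**Step 1: can 7.4 be triggered by contamination?** The expected result of both external levels (10,000 and 1,000 ge copies/mL) is positive. Added YFV template leaves a positive result positive. Section 7.4 sets no quantitative range for the control. Read as a positive/negative rule, it flags contamination with probability 0.

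**Step 2: does anything else in the protocol serve as a negative run control?**

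| Candidate | Where | Why it does not close the gap |
|---|---|---|
| Serum with uninfected culture medium | 7.3 | Proficiency panel only, completed before evaluation testing starts |
| YF-negative specimen | 6.2 | Member of the precision set; no run-validity role and no precision row in Table 1 |
| Internal controls | 7.1 | Check extraction, amplification or detection, not absence of YFV |
| Non-YFV members of the QCMD panel | 5.4 | Named for specificity; 7.2 specifies the two 17D levels |
| Manufacturer instructions | 6.1 | Might ask for a user-supplied negative; the protocol does not |
| Clinical negatives | 5.5, 6.4 | These are the outcome being scored, so using them to judge the run would be circular |
| Re-testing | 8.4 | Results are described; no rule voids a contaminated run |

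**Step 3: what would a negative control detect?** Assume a fraction q of the wells in a run is contaminated at random. With m negative controls, P(run flagged) = 1 − (1 − q)^m.

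| q (assumed) | m = 0 (as written) | m = 1 | m = 2 |
|---|---|---|---|
| 1% | 0 | 1% | 2% |
| 10% | 0 | 10% | 19% |
| 50% | 0 | 50% | 75% |
| 100% (e.g. contaminated reagent) | 0 | 100% | 100% |

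The gain is large for gross or reagent contamination and small for isolated wells.

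**Step 4: how exposed are the two decisions?**
- *Clinical negatives.* The panel adds up: 10 + 10 + 80 = 100. With 80 negatives and no false positive allowed, a perfectly specific assay fails with probability 1 − (1 − c)^80, where c is the contamination rate per specimen. The documents give no value for c. At assumed rates of 0.1%, 0.5%, 1% and 2% the probability is 0.0769, 0.3304, 0.5525 and 0.8014. This shows how strict the criterion is. It does not measure the gain from the fix, because independent single-specimen events are the kind that Step 3 shows one control mostly misses.
- *LoD.* With five replicates per level, one false detection raises the observed detection rate at that level by 1/5 = 20 percentage points, in the direction of a lower estimated limit. The shift in the estimate would depend on the contamination rate and the assay's detection curve, and the documents give neither.

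**The case against.** The strongest case against is one of reach and size, and much of it stands.

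- **Reach.** Only kits without a negative control are affected, and nothing says that such a kit is under evaluation. Annex 1 item 10 records positive and negative controls as separate yes/no entries, so it allows for such kits without showing that there are any.
- **Actual practice.** The work is done by an accredited laboratory under controlled procedures, and manufacturer instructions apply. A negative control may well be run. A reader might infer that these runs will have none; the documents support only that the protocol does not require one or tie it to run validity.
- **Visibility.** Gross contamination of the clinical panel would appear as several unexpected positives among 80 blinded negatives, so it would not necessarily go unnoticed. But there is no rule for acting on it, and the results would still be scored against expectation. The LoD panel has no comparable set of negatives.
- **The single-well example.** One contaminated negative gives 79/80 = 98.75% (exact 95% CI 93.2% to 99.97%) and fails the 100% rule. A reader might take this as the cost of the gap. It is not: any single false positive, whatever its cause, gives the same figure, and one negative control would usually miss that event.
- **High-titre carry-over.** A reader might also picture material at 10^5 ge copies/mL beside clinical negatives. The documents do not support this: spiked clinical specimens are at 5000 ge copies/mL, the 10^5 material belongs to the precision set, and no section says that panels share runs.

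None of this makes the substitution rule work: a positive specimen still cannot stand in for a negative control.

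**Conclusion.** The concern holds in a limited form. For kits supplied without their own controls, 7.1 and 7.2 together require no negative run control, and 7.4 as written cannot be triggered by YFV contamination. This is a stated rule that cannot do its job, not a detail left for later. It matters because the 100% rule for negatives and the LoD listing threshold both assume valid runs.

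The size of the effect cannot be derived from the document. The direction can: against the assay in the clinical panel, in its favour in the LoD panel. The conclusion rests on reading the expected control result in 7.4 as positive or negative, and it applies only where a kit lacks a negative control. Section 7.1 also leaves unclear what happens when a kit supplies a positive control but no negative one. The point should be corrected before such a kit is tested; it does not call the whole evaluation into question.

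**What to change.** - **7.2:** add a YFV-negative external control, namely the serum with uninfected culture medium already prepared for 7.3, taken through extraction in every run of a kit that lacks a negative control.
- **7.1:** state that this specimen replaces a missing kit negative control, including when the kit supplies only a positive one.
- **7.4:** state that a positive result in it makes the run invalid and the run is repeated.
- **8.1:** count such runs among the invalid runs.

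The cost is about one extra test per run, some more of the 7.3 material, and an update of the 310 tests estimated in section 10. The number of runs is not stated, so the total cannot be given here. The limit should be acknowledged in the text: one negative control detects widespread contamination but not most single-well events (10% of runs flagged when 10% of wells are affected; 19% with two controls).

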## 7.2 External quality control specimen

The evaluating site will run a validated external control specimen. This external quality might be available from a commercial source (EVA, QCMD, see above). The 17D standard preparation in a medium (10,000 ge copies/mL) and low (1,000 ge copies/mL) concentration spiked in a YF negative test human serum should be used.

## 7.3 Proficiency panels

A proficiency panel of 10 specimens comprised of the three YFV strains (17D, African and South American wild type strain) at high (100,000 ge copies/mL), medium (10,000 ge copies/mL) and low (1,000 ge copies/mL) concentrations and serum spiked with media from uninfected cell culture (negative control);. This panel must be run successfully for each assay by each operator before the evaluation.

## 7.4 Limits of acceptability

All results on test kit controls and the external control specimen will be documented. If the control sample does not give the expected result, the run will be considered invalid, and the run will be repeated. All problems shall be recorded on a data sheet. The principle investigator will be responsible for carefully checking all data entry forms for legibility, accuracy and completeness.

## 7.5 Interpretation of results

The interpretation of results for each assay under evaluation is made according to the manufacturers’ instructions. Invalid test results and errors must be recorded. Recording will be done either directly via printer or manually in the data collection sheet. In order to avoid transcriptional errors, the four-eyes principle has to be performed. For safety reasons a digital record of the results will be kept.

# 8. Analysis of data

## 8.1 Invalid runs

The number of invalid test runs will be recorded as the absolute number of invalid runs and as a percentage of the total number of runs performed for the entire evaluation using all specimens.

## 8.2 Invalid results (invalid internal quality control (IQC)/calibrator)

The number of invalid specimens’ results is recorded. They are presented as a percentage of the total number of specimens tested per platform for the entire evaluation.

If applicable, other types of readings indicating an invalid result (e.g. error) will also be recorded and reported as a percentage of the total number of specimens tested of the entire evaluation.

## 8.3 Analytical Sensitivity and Specificity

The limit of detection (LoD) is the lowest concentration of analyte that can be consistently detected in at least 95% of specimens tested under routine laboratory conditions and in a given specimen matrix. It defines the analytical sensitivity. The sensitivity and LoD will be estimated using the Probit analysis on the results of the five replicates of the LoD panel.

An acceptance criteria for the lower performance limit of the assay shall be ≤1000 ge copies/mL. Assays that do not reach this LoD will not be considered for listing by the WHO.

The results of testing for each individual analyte should be reported separately. Where unexpected results have been encountered, these should be noted in the report

**8.4 Clinical Performance**

For the estimation of sensitivity and specificity of the assay under evaluation for the detection of YF nucleic acids, the results of the assay under evaluation will be compared to the expected result.

Specificity will be calculated as the proportion of true negative specimens identified by the index method compared to all negatives by the reference method. Specificity will be expressed as a percentage.

Sensitivity and specificity will be estimated with their 95% confidence intervals. The 95% confidence intervals are calculated in order to assess the level of uncertainty introduced by sample size. Exact 95% confidence intervals for binomial proportions will be calculated from the F-distribution.

The initial and re-testing results of specimens (undertaken in accordance with manufacturers instructions) will be described in the report.

# 9. Report preparation

WHO will produce a draft of the results, which will be shared with the evaluating laboratory and the manufacturer.

Manufacturers will have one-month right of reply. After one month the report will be accepted as final by WHO. The final report will be prepared and disseminated by WHO. A copy of the final report will be sent to the authorized contact designated by the manufacturer and to the laboratory.

# 10. Materials and supplies

Manufacturers will provide the products and any equipment necessary for the evaluation free of charge. According to Table 1 the number of tests to be performed for this evaluation is estimated at 310 single tests.

# Annex 1. Assessment of operational characteristics

Date:

Name of assay       Name of operator

| General information | | | |
| --- | --- | --- | --- |
| 1 | What is the stated intended use of the assay? |  | |
| 2 | What is the principle of assay? |  | |
| 3 | What is the target of the assay? |  | |
| 4 | What is the region of amplification targeted by the assay? |  | |
| 5 | Which extraction method was used? Provide details | Automatic  Semi-automatic  Manual | |
| 6 | What is detection method of the final product? | End-point  Real-time | |
| 7 | What is the specimen volume required to perform the test? |  | |
| 8 | Which specimen types are compatible with the assay? | Serum  Plasma  Specify anticoagulant:  Whole blood  Other  Specify:  State the specimen type used: | |
| 9 | What is the test kit size evaluated (number of tests per kit)?  Which other test kit sizes are available? | tests/kit       tests/kit | |
| 10 | Controls included:  - Decontamination (Uracil-N-glycosylase [UNG])  - Positive (provided by manufacturer)  - Negative (provided by manufacturer)  - Internal controls (added to every specimen)  - External QC specimen + monitoring (provided by external source i.e. not the manufacturer) | YES  NO  YES  NO  YES  NO  YES  NO  YES  NO | |
| Operational aspects | | | |
| 11 | Are instructions for use concise and clear for:  the assay?  the extraction platform?  the amplification platform?  - What instruction language options are available? | | YES  NO  YES  NO  YES  NO  English  French |
| 12 | What is the total number of tests per run?  How many specimens can be tested per run?  How many controls are required per test run? | | Total Tests:  Patient Specimens:  Controls required: |
| 13 | What is the necessary time to obtain first result starting after specimen preparation. | | hours;      min |
| 14 | What is the hands-on time for the technician performing the assay? | | hours;      min |
| 15 | Technical skills required of staff:  -Reconstitution of reagents/buffers required  -Calculation of dilutions  -Number of steps required | | YES  NO  YES  NO  Number of steps: |
| 16 | How many days of training (by the manufacturer) are required to perform the assay? | | days |
| 17 | What is the rate of invalid runs during the evaluation period?  What is the rate of invalid individual results over the evaluation period? | |  |
| 18 | What is the level of automation of the platform, including the extraction component? | | |
| 19 | Having considered the elements above, assign a level of difficulty/complexity to the performance of the assay from specimen preparation to result (including analysis of the results):   \| Extremely Simple Very Complex \| \| \| \| \| \| --- \| --- \| --- \| --- \| --- \| \|  \|  \|  \|  \|  \| \| 1 \| 2 \| 3 \| 4 \| 5 \| | | |
| Reagents storage, specimen transport, processing and storage | | | |
| 20 | What is the shelf life upon manufacture of the reagents required to perform the assay? | | months |
| 21 | What is the claimed in-use stability of reagents once they have been opened? | | months |
| 22 | What are the specimen transport conditions required? | |  |
| 23 | Specimen processing procedure: | | |
| 24 | What are the specific storage conditions for :  -specimens?  -reagents?  -equipment? | | |
| Equipment and consumables | | | |
| 25 | Specify the dedicated equipment needs: | | |
| 26 | What general laboratory equipment is required to perform the assay but is not provided (e.g. vortex, waterbath, heating block, etc.)? | | |
| 27 | What are the reagents required to perform the assay but are not provided? (e.g. Fungicide, bleach, DNA/RNA decontamination products, ethanol): | | |
| 28 | Which laboratory consumables are required to perform the assay but are not provided (e.g. pipette tips, tubes, etc.)? | | |
| Infrastructure | | | |
| 29 | Dimensions & weight of equipment (metric system) | | - Extraction unit:  - Amplification:  - Detection unit: |
| 30 | What is the platform type? | | -Freestanding  - Bench top  -Other: |
| 31 | What are the dimensions of test kit (reagent pack)? | |  |
| 32 | Infrastructure (mechanical/power, physical, environmental)  -What are the voltage requirements?  UPS, brownouts, blackouts  - Is a temperature controlled room (air-conditioned) required?  -Is a dust-free environment required?  -Are there any altitude or humidity specifications?  -Distilled/deionised water requirements | | Voltage:  YES  NO  YES  NO  Altitude:       Humidity: |
| 33 | What are the requirements for separation of workspace? (e.g. specimen processing, extraction, amplification) | |  |
| Waste disposal and biosafety | | | |
| 34 | What are the waste volumes produced per run?  Does disposal of the consumable pose a substantial infection risk? | | Volume:  YES  NO |
| 35 | Are there any safety concerns for the user?  -Biological hazard (consider specimen collection, specimen processing eg centrifugation, hardware contamination, aerosol production, wastes)  -Chemical hazards (e.g. for extraction methods): | | YES  NO  YES  NO  YES  NO  Specify: |
| Calibration, maintenance and troubleshooting | | | |
| 36 | Is daily calibration of the instrument necessary? | | YES  NO  If answer is NO, specify frequency: |
| 37 | What is the maintenance frequency required for the equipment? (e.g. Fungicide treatment, bleach treatment, RNA decontamination, ethanol, UV-irradiation) | | Daily  Weekly  Monthly  Yearly  No need |
| 38 | What was the frequency of breakdown/blockage over the study period? | | None  1-5 times  > 5 |
| 39 | What was the response time of the instrument technician/engineer after notification of the instrument's breakdown? | | Same day  1-2 days  3-5 days  >5 days |
| Data Management | | | |
| 40 | What is the system for data collection and storage?  and compatibility/interfacing with LIMS | | |
| 41 | Is a printer required? | | YES  NO  If YES, is it provided? YES  NO |
| 42 | What language options are available for the software and results? | | English  French |
| Final Appraisal, Comments | | | |
| 43 | Having considered all the elements above, does the technician in charge of the evaluation consider the assay to be   \|  \|  \|  \|  \|  \| \| --- \| --- \| --- \| --- \| --- \| \| 1 \| 2 \| 3 \| 4 \| 5 \| \| Poor \| Needs Improvement \| Satsfactory \| Good \| Excellent \| | | |
| 44 | What are the advantages of this platform?    What are the disadvantages of this platform?    Other comments: | | |
